#### Strategies to improve adherence to interventions {11c}

To ensure retention of participants, follow-up visits will be scheduled to coincide with routine clinic appointments as far as possible. Moreover, we attract the participants through regular biweekly TCM health lectures in each clinical trial center. In addition, study staff will contact participants, either over the phone or WeChat, before their scheduled follow-up appointment. Finally, participants will receive reimbursement for their time and transportation in the form of a gift card.

#### Relevant concomitant care permitted or prohibited during the trial {11d}

In principle, other pain killers, muscle relaxants, and other drugs are not allowed to be used during the trial. If there is any special situation, it must be used, and the use situation needs to be truthfully recorded in the medication registration form. The patients with other diseases before enrollment will continue to maintain the original treatment after enrollment, and the medication related to pain shall be recorded in the medication record form. When the case falls off or the patient’s compliance is poor, the reasons for the fall off and poor compliance shall be entered in the case observation form in detail, and the patient’s understanding and support shall be obtained by contacting the patient as frequently as possible; the evaluation items that can be completed shall be completed, and the last treatment time shall be recorded. The case fall off, the patient’s compliance, and adverse reactions shall be statistically described and compared and evaluated between the groups.

#### Provisions for post-trial care {30}

Once participants complete the study, they will be able to continue receiving clinical care from respective clinical trial centers, for example, TaiChi, Baduanjin, characteristic cervical function training guidance techniques of TCM. Participants study records will be reviewed if necessary. For the patients who have completed the trial but have no effect on remission, doctors should provide alternative treatment, such as combined traction, acupuncture, and other comprehensive conservative treatment, as well as the application of analgesics and muscle relaxants. When the sleep patterns and quality of life of the patients are seriously affected, patients can be identified as inpatients for further treatment, including nerve block injection, surgery, and other treatments.

#### Outcomes {12}

##### Effectiveness evaluation index

The manual intervention program was pre-tested in our research group’s experimental study and was in effect immediately after the shortest treatment, and the longest treatment time was 12 weeks. Combined with the reported literature on related neck pain [14, 15], both groups are treated according to the main intervention methods of each group for a period of up to 12 weeks. Clinical data will be collected before the intervention and immediately after the first treatment; at 3 days and 1, 2, 4, 8, and 12 weeks after the intervention; and at 26 and 52 weeks after treatment follow-up of clinical observation index data collection. The clinical observation indexes are as follows: (1) cervical pain is the primary observation index, measured by NRS [16] and composed by a horizontal line with a length of 0–10 cm, and the anchor words are “0” for “no pain” and “10” for “extreme pain.” Participants are asked to select a point on the NRS line segment that corresponds to their current or recent week’s average pain intensity and draw a vertical line as a marker to express the pain intensity. The researchers determine the NRS score by measuring the distance from the starting point of “painless” to the marker point; the higher the score is, the stronger the degree of pain is. The specific judgment is as follows: 1–3 cm is mild pain, 4–6 cm is moderate pain, and 7–10 cm is severe pain. The secondary indices include the following: (2) cervical dysfunction index, measured by patient self-evaluation with cervical NDI [17, 18], which has 10 items in total, six options under each item, from light to heavy, corresponding to the score of 0–5, the lowest score of each item is 0, and the highest score is 5; the higher the score is, the more serious the degree of dysfunctions. NDI (%) = [(total score)/(number of items completed by subjects × 5)] × 100. The specific judgment is as follows: 0–20% indicates mild dysfunction, 21–40% indicates moderate dysfunction, 41–60% indicates severe dysfunction, 61–80% indicates extremely severe dysfunction, and 81–100% indicates complete dysfunction (whether subjects have exaggerated symptoms should be checked in detail); (3) cervical activity measurement [19], measured by the cervical vertebra mobility measurement program of Android mobile phone system, with a minimum of 5 degrees carry measurement; (4) overall improvement, measured by self-evaluation of patients with SF-36 (The Medical Outcomes Study 36-Item Short-Form Health Survey) [20, 21], which is composed of physical functioning, role-physical, bodily pain, general health, vitality (VT), social functioning (SF), role-emotional, mental health, and health transition; and (5) satisfactory treatment, determined by patient self-evaluation, is 1 of 3 levels: dissatisfied, satisfied, and very satisfied.

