### Inclusion criteria

Age range from 18 to 65 years.The subjects meet the above diagnostic criteria for acute and subacute neck pain.NRS score of ≥ 3.It is an axial (non-root) neck pain caused by changes in the facet joints, discs, muscles, and ligaments [1].Those who are willing to participate in this experiment and sign the consent letter.

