### Interventions

#### Intervention description {11a}

##### Trial group

The main intervention method in the trial group is Shi’s cervical manipulation therapy. The manipulation treatment team is composed of six clinicians (two in each of the three trial centers) with a minimum of 5 years’ experience in manual operation, who are good at manual spine diagnosis and treatment and have received standard operating procedures (SOP) training in this study. Each selected subject should have a 3-dimensional (3D) computed tomography (CT) reconstruction of the cervical vertebra, as well as a special physical examination of the cervical vertebra. Each subject will receive an initial diagnosis for 15–20 min after entering the group, including brief history collection, cervical static palpation (tenderness point and muscle spasm), cervical dynamic palpation (intervertebral looseness of the cervical spine), cervical sequence activity inspection, and cervical nerve reflex. Both history and examination results should be recorded in the case report form. According to the examination results, manipulation clinicians will give a comprehensive diagnostic analysis and manipulation therapy to each subject’s cervical spine. Key points of manipulation therapy operation are as follows: (1) acupoint pressing analgesia operation, according to the treatment principle of local acupoint selection and remote acupoint selection of cervical vertebra; point rubbing; and pressing operation are performed on the thumb pulp. The pressure can be light to heavy, then heavy to light, and the operation is repeated. The specific strength is to press until thumb nail color is white, while considering patient tolerance. Each acupoint is operated for 1 min. The specific acupoints are as follows: (a) local acupoints—Fengchi (International acupoint code GB20), Fengfu (International acupoint code DU16), Tianzhu (International acupoint code Bl10), Wangu (International acupoint code GB12), Dazhui (International acupoint code DU14), Jianjing (International acupoint code GB21), Jianzhongshu (International acupoint code SI15), Quepen (International acupoint code ST12), Tianzong (International acupoint code Si11), and Ashi; (b) remote acupoints—Lieque (International acupoint code LU7), Houxi (International acupoint code SI3), and Hegu (International acupoint code LI4). (2) Bone-setting manipulation operation, according to the results of palpation and 3D CT reconstruction of the patient’s cervical spine, the clinicians will give directional and fixed-point bone-setting manipulation to treat the cervical vertebrae semidislocation. The specific operation is as follows: the patient sits on the treatment chair, with the head slightly bent forward, and the manual operation physician stands at the patient’s side, with the right side as the patient’s side, for example, the manual operation physician locks his left thumb against vertebral plate between the transverse process and the spinous process of the cervical vertebra with semidislocation, and the other four fingers stick to the patient’s left head and neck, and the middle and upper part of the elbow of the right arm slightly bent on the patient’s lower jaw, according to the vertebrae semidislocation direction, the left thumb with pushing force to the vertebral plate in the opposite direction of semidislocation, while the right forearm rotates rapidly to lift and rotate the head with a direction- and size-controlled flashing force. There is a sliding motion and snapping sound from the vertebra under the left thumb. The whole manual operation treatment lasts for 20 min each time, and is done twice a week, with the longest course of treatment lasting for 12 weeks.

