#### Statistical methods

##### Statistical methods for primary and secondary outcomes {20a}

Statistical results and data analysis are the responsibility of the researcher (Statistics Center) in charge of statistics and data analysis for the entire project, and the patients are divided into the following data sets according to different situations.

Full analysis set refers to the ideal set of subjects as close as possible to the intentional analysis principle (mainly including all randomized subjects). The data set is obtained after the elimination of the smallest and reasonable method among all randomized subjects. To estimate the missing value of the main variable, the last observation carried forward (LOCF) method is used to carry forward the missing part of the test data. The number of subjects in each group who evaluate efficacy at the end point is consistent with that at the beginning of the test.

Per-protocol set, all patients who meet the trial protocol, who use 80–120% of drugs, have good compliance, do not use prohibited drugs during the trial, and complete the CRF requirements.

Safety analysis set, all cases are randomly divided into groups, at least one use of study drug, or receive manual treatment, and at least one follow-up record, constitute the safety analysis population of this study. Safety population is the main population for safety evaluation in this study.

The main variables and the comprehensive efficacy analysis are the full analysis set and the compliance scheme set, respectively; the demographic and other baseline characteristics are the full analysis set; the safety evaluation is the safety set.

For continuous variables, the number of cases, mean, standard deviation, median, and minimum and maximum values will be listed; for classified variables, the form of frequency table (frequency and percentage) will be listed. Baseline is defined as the last observation data before the first treatment.

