Specific statistical data analysis, using the latest SPSS statistical analysis software, first of all, paired *t* test statistical analysis is carried out for each group’s pre-treatment pain and the improvement of each group’s pain after treatment intervention, and single-factor analysis of variance is carried out for each group’s immediate, 3-day, 1-, 2-, 4-, 12-week pain after intervention; secondly, before treatment and immediately after treatment intervention, 3 days, 1, 2, 4, and 8 weeks. One-way ANOVA is used to analyze the cervical dysfunction index, cervical activity, overall improvement, and treatment satisfaction of patients at 12 weeks. All the statistical tests are double-sided, *P* < 0.05 would be considered statistically significant.

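### The primary NRS may be scored as current pain or as the past week's average, with neither assigned to a visit; under the week-average option the immediate and day-3 scores are mostly pre-treatment pain

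*Protocol article*

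**What the plan says.** The Effectiveness evaluation index section states that "cervical pain is the primary observation index, measured by NRS" on a 0–10 cm line. Participants mark the point that "corresponds to their current or recent week’s average pain intensity". The same section sets the schedule: "Clinical data will be collected before the intervention and immediately after the first treatment; at 3 days and 1, 2, 4, 8, and 12 weeks", with further follow-up at 26 and 52 weeks.

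The early scores are formally analysed. Section {20a} plans paired t tests of pain before against after treatment, and says that "single-factor analysis of variance is carried out for each group’s immediate, 3-day, 1-, 2-, 4-, 12-week pain after intervention".

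Two other places use the same scale without a recall period. Section {20a} says "Baseline is defined as the last observation data before the first treatment", and the Inclusion criteria require "NRS score of ≥ 3". The Sample size section {14} is built on the NRS at 12 weeks.

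**The concern.** Current pain and a week's average are different measurements. In patients whose symptoms have lasted less than 12 weeks, pain may well be changing within the week, so the two need not agree. One instruction offers both and ties neither to a visit, so two problems follow.

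- A participant may answer one way at baseline and the other way later. The paired difference then contains the gap between the two recall periods as well as any change in pain.
- A one-week window does not fit an assessment made minutes or three days after treatment starts, because most of the window lies before treatment. The article reports from its own pre-testing that the manipulation works immediately after the shortest treatment. The immediate and day-3 tests are where that would be seen, and the week-average option is least able to show it there.

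**Working it through.** The plan gives no figure of its own on this point, so there is none to reproduce. The check is on the recall window.

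**Inputs from the article.** Recall window under the week-average option: 7 days. Assessment times: immediately after the first treatment, day 3, then weeks 1 to 12. Session length: "The whole manual operation treatment lasts for 20 min each time".

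**Pre-treatment share of a 7-day average** taken t days after treatment starts = max(0, 7 − t)/7.

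- Immediate: t = 20 min; 7 days = 10,080 min; (10,080 − 20)/10,080 = 99.8%.
- Day 3: (7 − 3)/7 = 4/7 = 57.1%.
- Week 1 and later, including week 12: 0%, provided the week-1 visit is not held before day 7.

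If pain falls at once by D and then stays level, the week average shows 1 − share of that fall: about 0% of D at the immediate assessment and 3/7 = 43% of D at day 3. Under the current-pain option the share is 0% at every post-treatment visit.

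**Paired comparisons.** Let g be the gap between week-average and current pain in the same participant at baseline. With baseline scored as the week average and follow-up as current pain, recorded change = true change + g. The article gives no value for g.

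**Illustration of the early tests.** The article gives no early-visit figures, so I assume that its week-12 values apply there: difference 2.08 − 1.50 = 0.58 and SD √[(1.70² + 1.65²)/2] = 1.675. I also assume 120 analysed per arm, a two-sided 5% test, and a fraction f of participants in both arms using the week average. Retained difference = 0.58 × (1 − f × share).

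| f | Day-3 difference | Day-3 power | Immediate difference | Immediate power |
|---|---|---|---|---|
| 0 | 0.58 | 76.5% | 0.58 | 76.5% |
| 0.5 | 0.41 | 48% | 0.29 | 27% |
| 1 | 0.25 | 21% | about 0 | none of use |

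The 76.5% is the reference for this illustration only. How it compares with the planned power is a separate question.

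**If the choice differs by arm (day 3).** With no true difference between arms, the spurious difference per 1-point fall in pain is (f₂ − f₁) × 4/7. That is 0.11 for 40% against 60% using the week average, and 0.29 for 25% against 75%. These fractions are assumed; the article does not show that the choice differs by arm.

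**The case against.** The strongest reply is that the harm is conditional. The same sentence offers current pain, the natural answer minutes after a first session, and with it the carry-over disappears. The case report form, operating procedures and investigator manual may fix the wording by visit, and Fig. 2 is not shown. This stands as a limit: one cannot say that the immediate and day-3 tests necessarily fail to measure early relief. It does not remove the point, because the printed definition offers both options without assigning either.

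The carry-over also misses week 12, on which the trial is sized. That stands in full.

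A reader might go further and infer that current scores in the manipulation arm capture short-lived relief after a session, biasing every visit including week 12. The documents do not support this. The section on adherence says only that "follow-up visits will be scheduled to coincide with routine clinic appointments as far as possible"; it does not mention manipulation sessions, and nothing says that the NRS is recorded after one. Treatment lasts up to 12 weeks, so some patients may have no session at week 12 and none are scheduled at 26 or 52 weeks. Any size put on such a bias would rest on assumed inputs alone.

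Finally, recruitment was expected to end by 31 December 2020 and the article appeared on 8 February 2021. On that timetable the baseline, immediate and day-3 scores are largely collected, so a change of wording comes too late for most of them. This is fair, and the fix has to provide for it.

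**Conclusion.** The point holds in a limited form. The primary NRS has two recall periods and no rule for choosing between them, so baseline and follow-up scores may be different quantities. Where the week average is used, the immediate score is about 99.8% pre-treatment pain and the day-3 score 57%. These shares need only a 7-day window and the printed schedule; reading them as 0% and 43% of D also assumes an immediate fall that persists.

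From week 1 on, including week 12, there is no carry-over. Mixing adds noise there, and bias only if the choice of recall differs by arm or between baseline and follow-up, which the documents do not show. The sample size is unaffected. The definition should be corrected, but the week-12 comparison is not shown to be biased.

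**What to change.** State one recall period per visit.

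- Past-7-days average: at baseline and at weeks 1, 2, 4, 8, 12, 26 and 52.
- Pain right now: at baseline, immediately after the first treatment and at day 3.
- Compare each follow-up score only with the baseline of the same recall.
- As a precaution, record the NRS before any same-day session, except at the immediate assessment.

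For data already collected under the mixed wording, use the recall where it was recorded at the time. Where it was not, report the immediate and day-3 results as descriptive.

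The cost is a protocol sentence, a line on the case report form and one extra NRS item at baseline. The downside is that scores collected before the change keep the old wording and cannot be repaired afterwards.

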
##### Safety evaluation index

During the test, we should observe whether there are adverse reactions and adverse events, and make records. If there are adverse events, such as adverse effects on patients’ consciousness, feeling, exercise, sleep, blood pressure, pulse, heart rate, respiration, and other normal physiological indicators, cervical fracture, skin damage, spinal cord and vertebral artery injury, gastrointestinal discomfort or ulcer, bleeding, and black stool, the occurrence of adverse reactions shall be recorded in detail on the case observation form, including the time, severity, duration, and treatment measures, and correlation with experimental treatment method shall be analyzed with comprehensive consideration of complications and combined treatment. In case of adverse reactions, the clinical observation physician can decide whether to stop the trial according to the patient condition. Patients who stop treatment due to adverse reactions should be tracked and investigated, and the results should be recorded in detail.

#### Participant timeline {13}

Participants in both groups are treated according to the main intervention methods of each group for a period of up to 12 weeks. Clinical data are collected before the intervention and immediately after the first treatment; at 3 days and 1, 2, 4, 8, and 12 weeks after the intervention; and at 26 and 52 weeks after treatment follow-up of clinical observation index data collection (see Fig. 1 for the participant timeline for the trial and Fig. 2 for the study assessments).

**Fig. 2 Fig2:**
[figure not shown]
Recommended content for the schedule of enrolment, interventions, and assessments. ^#^If the subject has had the relevant imaging examination within 3 months and can provide the report form, no additional imaging examination is required. *If the subjects were directly enrolled at the first visit, visit 1 and visit 2 coincided in time, and visit 2 index was taken as the baseline

#### Sample size {14}

In this project, the trial group and the control group are to be set up. This study is designed with the control group as the optimal design, and the results are summarized according to previous clinical trials and literature [2]. According to the results of previous clinical trials and literature summary, the first observation index after 12 weeks of treatment was NRS score of neck pain, 1.50 ± 1.70 in the trial group, 2.08 ± 1.65 in the control group; *α* = 0.05 (bilateral test), *β* = 0.10, boundary value 0.08, sample size ratio *k* = 1 in both groups. The PASS software is used to calculate the sample size of 102 cases in the two groups. Considering that the sample size loss rate is about 10–20%, further calculated the sample size of each group is *N* = 120.

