## Discussion

The purpose of this study is to confirm our hypothesis through clinical trials that Shi’s cervical manipulation has more advantages in the efficacy, safety, and satisfaction of acute and subacute neck pain than traditional NSAIDs.

To achieve the goal of the study, a multicenter, positive-controlled, randomized clinical trial, comparing traditional analgesic drugs (NSAIDs) for neck pain is used to evaluate and show that Shi’s manipulation is more effective, safe, and satisfactory in the treatment of acute and subacute neck pain.

According to the latest survey [1–3], 71.5% of the general population had neck pain for more than a year. Although neck pain caused only 1.7–11.5% of disability, it is worth noting that, equivalent to back pain, it caused a huge burden and disability rate on individuals and the social economy and was listed as 1 of 5 chronic and refractory diseases by the US government. With the continuous development of social life, the high incidence rate of neck pain is not only confined to developed countries such as the USA, but also affects the developing countries, and has become a worldwide urgent disease [22–24]. At present, the clinical treatment of neck pain is no more than surgical treatment and non-surgical treatment [25]. Various clinical case studies confirm that the long-term effect advantage of surgical treatment is very limited compared with non-surgical treatment [26–29]. The latest research shows that clinical management of neck pain should pay close attention to the active diagnosis and treatment of acute and subacute neck pain, in an attempt to and thwart its progression to chronic neck pain [1, 16, 30]. Previous clinical trials have confirmed that Western chiropractic manipulation, health education, family exercise, and drugs are the main non-surgical treatment measures for acute and subacute cervical pain [11, 31–33]. Chiropractic manipulation, which can effectively relieve patients’ neck pain and cervical dysfunction, has both short- and long-term effects with clinical advantages, while drug treatment generally extends the treatment course. Therefore, clinicians should pay more attention to the cost of treatment, adverse drug reactions, and patient acceptance [11, 30, 34].

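### The stated sample-size inputs do not give 102 per group, and power for the planned superiority comparison is about 76% at best, not 90%

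*Protocol article*

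**What the plan says.** All the inputs are in section {14} of the protocol article. The endpoint is the NRS neck pain score after 12 weeks, taken as 1.50 ± 1.70 in the trial group and 2.08 ± 1.65 in the control group. Alpha is "0.05 (bilateral test"), beta is given as "0.10, boundary value 0.08", and the allocation ratio is 1. The result is "The PASS software is used to calculate the sample size of 102 cases in the two groups". The section continues "Considering that the sample size loss rate is about 10–20" per cent and arrives at 120 per group, 240 in total. It does not name the hypothesis being sized or say what the boundary value is for.

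The aim is set elsewhere. The Objective {7} states a superiority hypothesis, and the Discussion repeats that the trial is meant to confirm that manipulation "has more advantages in the efficacy, safety, and satisfaction of acute and subacute neck pain than traditional NSAIDs". Section {20a} says "All the statistical tests are double-sided", with significance at P < 0.05. It describes no non-inferiority test and no margin. It names the full analysis set, with LOCF for missing values of the main variable, and the per-protocol set as the sets for the main variables.

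**The concern.** Beta of 0.10 means 90% power. A reader who sees that figure beside a superiority aim will take the trial to have a 10% chance of missing its own assumed effect. If the true chance is two to three times that, a null result would be read as stronger evidence against an advantage than it is. The unexplained boundary adds a second difficulty: it belongs to a non-inferiority or superiority-by-margin design, and neither is described in the plan. This is a matter of figures that are stated and do not agree, so it is not detail that a fuller protocol or analysis plan could be expected to supply.

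**Working it through.** **Inputs (section {14}).** Difference 2.08 − 1.50 = 0.58. Pooled variance (1.70² + 1.65²)/2 = 2.806, so SD = 1.675. Two-sided alpha 0.05 gives z = 1.960; 90% power gives z = 1.282; 80% power gives z = 0.842.

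**Formula.** n per group = 2·SD²·(z_alpha + z_beta)²/d², where d is 0.58 for superiority, 0.58 + 0.08 = 0.66 for non-inferiority with margin 0.08, and 0.58 − 0.08 = 0.50 for superiority by 0.08.

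**Attempt to reproduce 102 at the stated two-sided 0.05 and beta 0.10.**

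| Hypothesis | d | n per group (normal) | n per group (t) |
|---|---|---|---|
| Superiority | 0.58 | 175.3 → 176 | 177 |
| Non-inferiority, margin 0.08 | 0.66 | 135.4 → 136 | 137 |
| Superiority by 0.08 | 0.50 | 235.9 → 236 | 237 |

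None is 102. One-sided alpha 0.05, which the section rules out, still gives 143, 111 and 193 at 90% power. Reading 102 as a total (51 per group) gives 41% superiority power and cannot lead to 120 per group, since 51/0.8 is only about 64. So 102 must mean per group.

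**Changes to a single input that do reach 102, or nearly.**
- Non-inferiority, margin 0.08, two-sided 0.05, power 80% instead of 90%: 101.1 → 102 (t: 103).
- Non-inferiority, two-sided 0.05, power 90%, margin 0.18 instead of 0.08: d = 0.76, giving 102.1. At n = 102 the power is 89.7% by the noncentral t.

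Changing two inputs also comes close: superiority with one-sided 0.05 and 80% power gives 103.1 → 104, or 100.1 → 101 with SD 1.65. That contradicts the stated two-sided test and makes no use of the boundary.

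**Power of the planned two-sided superiority comparison** (difference 0.58, SD 1.675).

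| Analysed per group | Normal | Noncentral t |
|---|---|---|
| 120 (all randomised) | 76.5% | 76.2% |
| 108 (10% loss) | 72.1% | 71.7% |
| 102 | 69.6% | 69.2% |
| 96 (20% loss) | 67.0% | 66.5% |

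**Difference detectable at 90% power**, as SD·√(2/n)·(1.960 + 1.282): about 0.70 at 120, 0.74 at 108, 0.76 at 102 and 0.78 at 96. The assumed difference is 0.58.

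**Loss allowance.** 102/0.90 = 113.3, 102/0.85 = 120 and 102/0.80 = 127.5. The 120 corresponds to 15% loss.

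**The case against.** Several points on the other side have weight.

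- **Analysis set.** Section {20a} keeps randomised subjects in the full analysis set through LOCF, so about 120 per group would be analysed even with dropout. This stands. The leading power figure is therefore 76%, and 66.5–72% describes only a set reduced by the stated loss. It does not restore 90%.
- **Which input is wrong.** Because 102 matches an 80%-power non-inferiority calculation, a reader might infer that the trial was really sized that way and that beta is the misprint. The match is close, but a margin of 0.18 at 90% power fits almost as well. The document does not settle it.
- **No hypothesis named.** Section {14} does not itself claim 90% power for superiority; it lists beta beside a boundary value. That is right, but the superiority aim and the two-sided tests are stated elsewhere, so the mismatch remains.
- **Loss rate.** A reader might call 120 an arithmetic error because it falls short at 20% loss. The stated range is approximate and 120 is exactly its midpoint, so this is a planning choice.
- **Non-inferiority claim.** A reader might suspect a later switch to non-inferiority. Nothing in the document plans one; the boundary is simply unexplained.
- **Exploratory label.** The Study setting {9} and the Discussion call the study exploratory or preliminary, and the Discussion lists small sample size as a limitation. This tempers over-reading, but it does not correct the power figure, and the Abstract and Discussion also speak of confirming the hypothesis.
- **Baseline adjustment.** Cutting about 175 to 102 would need a baseline correlation of about √(1 − 102/175.3) = 0.65. No such correlation or covariate is stated; {20a} lists paired t tests and one-way ANOVA.

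**Conclusion.** The concern holds. At two-sided 0.05 and beta 0.10, the stated means, SDs and boundary need 176, 136 or 236 per group according to the hypothesis, never 102. For the superiority comparison that the trial sets out to make, power for a difference of 0.58 is about 76% with all 120 per group in the full analysis set, about 66.5–72% with 96–108 per group, and 69% at 102. The type II error is thus about 24% to 34%, against the stated 10%.

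These figures rest on the section's own means and SDs and an unadjusted two-group comparison at week 12. The 76% also assumes that carried-forward values keep the same mean difference and SD. The document does not establish which input is wrong, so the conclusion goes no further than this: the inputs and the result disagree, and the 90% does not apply to the planned comparison.

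**What to change.** In section {14}:

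1. Check the PASS output and reconcile beta, the boundary value and 102. Keep the original design inputs visible, with a note on which was misreported, so that the discrepancy is explained and not erased.
2. Write that 102 is per group.
3. Replace the implied 90% with the achieved superiority power for a difference of 0.58 (SD 1.675, two-sided 0.05): about 76% for the full analysis set at 120 per group, and about 66.5–72% for 96–108 evaluable per group. Add the difference detectable at 90% power: about 0.70 at 120 and 0.74–0.78 at 108–96.
4. State that the primary comparison is superiority and that no non-inferiority conclusion will be drawn from the 0.08 boundary.

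The cost is a reworded paragraph and a less favourable stated power. No patients, visits or tests are added.
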